#### Exclusions

• recruited outside UK

• adopted or fostered children and children who have emigrated

Children who have been adopted or fostered will not be followed-up to avoid potential distress to parents and child. Children born in Scotland, Northern Ireland or Wales have different National Tests to England and therefore will not have data collected to assess educational achievement.

### Postal parent-report questionnaire

A parental questionnaire will be administered to determine the level of disability (severe, moderate, mild, none). This is based on the Multi-Attribute Health Status (MAHS) Mark II and III [14] classification system developed and widely tested by the Departments of Paediatrics and Clinical Epidemiology and Biostatistics of McMaster University, Canada. The additional domain of behaviour is being assessed using the strengths and difficulties questionnaire developed and validated by Robert Goodman [15]. Additional questions will assess the other health related outcomes. Deaths will be categorised hierarchically using the system below developed by PMG and with the advice of [name], Consultant Pathologist, John Radcliffe Hospital, Oxford

### Death categorisations

1. Congenital abnormality

2. Cancer/Neoplasia

3. Complications of Prematurity

3a. Chronic lung disease

3b. CLD and CNS

3c. Central Nervous System related to prematurity

4. Central Nervous System

5. Infection

6. Miscellaneous

7. Sudden Unexpected Death in Infancy (SUDIs, SIDS and Unascertained)

### National Tests

In England we will employ a unique and innovative approach of using the standard National Tests (Key Stage 1) to assess the children's educational ability supported by the Qualifications and Curriculum Authority (QCA). Dfes will provide anonymised data for test level achieved and ethnicity of all children in each treatment group. For those children for whom parental consent is obtained level data will be obtained from the Local Education Authority (LEA) and the scores for each question will be collected from individual schools. Children in Northern Ireland and Wales have different National Tests and no such tests are conducted in Scotland therefore these children will not have data collected to assess educational achievement.

### Estimated power of study

A total of 8942 babies survived until the end of data collection in England, Scotland, Wales and Northern Ireland. Of these, 4521 were in the SPL group and 4421 were in the PROM group. Not all of these babies will have survived until age 7 years; assuming an 85% response rate to a parental questionnaire, 3843 responses can be expected from the SPL group and 3758 from the PROM group (7601 in total).

Table 1 demonstrates the differences detectable between any two intervention groups for the listed primary measure (e.g. erythromycin vs. erythromycin-placebo) in each of the specified sub-groups (SPL and PROM). The estimates of prevalence of disability are based on data derived using the same instrument (MAHS Mark II) [14] on extremely low birth weight (ELBW) babies compared with a reference group of normal birth weight babies. As the majority of ELBW babies are born less than 28 weeks gestation they will have a higher prevalence of disability than the children included in the MRC ORACLE Children Study. For the measure of '3 or more attributes' affected, an incidence of 28% occurred in the ELBW group compared with 2% in the reference group. As the gestational age of the ORACLE population of children is between these extremes a conservative disability estimate of 5% has been taken as the principal estimate and sensitivity to variation of this value of the power of the study to detect differences is explored in the table. By ranking children into groups by their degree of disability (the number of attributes affected) the power of the study to demonstrate smaller differences will be increased by using tests for trends.

**Table 1 T1:** For each sub-group (PROM or SPL), a response from 3700 babies will allow the following differences to be detected with 80% power:

**Outcome**	Incidence in erythromycin group	Incidence in erythromycin placebo group	Relative risk reduction
**'3 or more attributes affected'**	**3.1%**	**5%**	**38%**
	5.6%	8%	30%
	1.5%	3%	50%

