### Primary & secondary outcomes

The primary outcome is:

1) the overall level of disability (severe, moderate, mild, none) derived from the Multi-Attribute Health Status (MAHS) classification system.

The secondary outcomes are:

1) number of children with 3 or more abnormal attributes derived from the MAHS classification system

2) degree of function (severe, moderate, mild, none) within the 9 domains of vision, hearing, speech, ambulation, dexterity, emotions, cognition, pain and self care.

3) behaviour (Goodman's strengths and difficulties questionnaire).

4) educational achievement in reading, mathematics and writing at Key Stage 1. Data on both levels and raw scores will be collected.

5) incidence of specific medical conditions:

• cerebral palsy

• epilepsy

• respiratory illness including asthma

• diabetes

• admission to hospital in last year

• other diseases

• death – from trial entry to aged 7 years

- from initial discharge from hospital to aged 7 years

• covariates – family demographic information (housing status, ethnic group, smoking practice) will be collected.

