### Analyses plan

The primary analysis will comprise comparison of MAHS disability prevalence by allocated treatment group, through fitting of logistic models including terms indicating allocation to Co-amoxiclav/not and to Erythromycin/not, together with an interaction term. Both HUI2 and HUI3 data will be collected and analysed as they have been designed to complement one another but are based on the same conceptual framework. HUI2 refers to worry and anxiety, HUI3 to happiness versus depression. Similarly while both refer to the degree of severity of pain, HUI2 focuses on the use of analgesia while HUI3 focuses on the disruption of activities. Self-care is only available in HUI2 and dexterity only in HUI3. Sensitivity analyses will include i) logistic modelling of the MAHS level of disability, ii) corresponding models for risk differences, iii) alternative approaches to analysing outcomes from multiple births, and iv) models adjusted for demographic covariates if their balance deteriorates during further follow up, and for other covariates including length of gestation, and year of KS1 assessment and original ORACLE outcomes.

Analyses of secondary outcomes will follow the approach for the primary outcome, appropriately modified where necessary to accommodate continuous or survival measures. Details of the analysis of KS1 data are to be developed in collaboration with colleagues in the agency responsible for collection and interpretation of these data. Explicit allowance for multiplicity of comparisons will be made in interpretation of the results.

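### The outcome, power and analysis sections disagree on the primary endpoint, so the stated 80% power belongs to an outcome listed as secondary

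*Protocol article*

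**What the plan says.** Three sections of the protocol article bear on the primary endpoint.

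- **Primary & secondary outcomes.** The single primary outcome is "the overall level of disability (severe, moderate, mild, none) derived from the Multi-Attribute Health Status (MAHS) classification system". The first secondary outcome is "number of children with 3 or more abnormal attributes derived from the MAHS classification system".
- **Estimated power of study.** "Table 1 demonstrates the differences detectable between any two intervention groups for the listed primary measure". Table 1 then has one outcome only, three or more attributes affected, at three control rates. The control rate comes from the same measure: "For the measure of '3 or more attributes' affected, an incidence of 28% occurred in the ELBW group compared with 2% in the reference group", and between those extremes "a conservative disability estimate of 5% has been taken as the principal estimate". The section adds that ranking children by the number of attributes affected and testing for trend would raise power, but gives no figure.
- **Analyses plan.** "The primary analysis will comprise comparison of MAHS disability prevalence by allocated treatment group", by logistic models with terms for each antibiotic and their interaction. Which levels count as disability is not said. Then: "Sensitivity analyses will include i) logistic modelling of the MAHS level of disability".

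**The concern.** A count of affected attributes and an overall severity grade are different variables. A child with one severely affected attribute ranks high on one and low on the other. The three-or-more measure cannot be both secondary outcome 1 and the primary measure that the power section says it has tabulated.

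The analysis section does not settle which is meant. Prevalence in a logistic model suggests a yes/no outcome. Because modelling by level appears separately as a sensitivity analysis, the four-level outcome seems not to be what the primary model uses. The prevalence could be any disability, moderate or severe disability, or three or more attributes.

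Two things are at stake. A reader who takes the 80% power as applying to the declared primary outcome is misinformed. And the document does not identify the result on which the trial's main conclusion will rest.

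**Working it through.** **1. Reproduce Table 1.** Inputs from the power section: 3700 responses per condition, 80% power, 3.1% v 5% in the principal row. Assumptions: two-sided 5% (neither alpha nor sidedness is stated), 1850 v 1850 at the factorial margin, independent children.

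Formula per group, with d the difference and p̄ the mean rate:

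n = [1.96·√(2p̄(1−p̄)) + 0.842·√(p₁(1−p₁) + p₂(1−p₂))]² / d²

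With p₁ = 0.031, p₂ = 0.05, p̄ = 0.0405 and d = 0.019:

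n = (1.96 × 0.2788 + 0.842 × 0.2785)² / 0.000361 ≈ 1689

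With continuity correction, n = 1793, or 3586 in total, a little under 3700.

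| Row | Power at 1850 v 1850, uncorrected | With continuity correction | Detectable rate at 80% power, corrected |
|---|---|---|---|
| 3.1% v 5% | 83.5% | 81.3% | 3.13% |
| 5.6% v 8% | 82.7% | 80.9% | 5.63% |
| 1.5% v 3% | 86.8% | 84.3% | 1.57% |

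Rows 1 and 2 reproduce; row 3 is somewhat conservative. With single factorial cells (925 v 925) the power would be only 54.5%, 53.6% and 58.5%, so the table rests on the factorial margins. Table 1 is therefore a yes/no calculation for three or more attributes affected.

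**2. Set the sections side by side.**

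| Section | Quantity treated as primary | Place of the alternative |
|---|---|---|
| Primary & secondary outcomes | four-level overall disability | three or more attributes is secondary outcome 1 |
| Estimated power of study | three or more attributes affected | four levels not mentioned; trend test is over number of attributes |
| Analyses plan | disability prevalence, cut not stated | level of disability is sensitivity analysis (i) |

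**3. Can a detectable difference for the four-level outcome be derived from the document?** No. It gives no expected split over severe, moderate, mild and none, and no control prevalence for any cut of that scale. What follows is illustration on assumed splits.

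For a proportional-odds model with N = 3700, V = (N/12)(1 − Σpᵢ³), and the detectable odds ratio is exp(−(1.96 + 0.842)/√V).

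- None/mild/moderate/severe 85/8/4/3%: Σpᵢ³ = 0.6147, V = 118.8, detectable odds ratio 0.773.
- 60/25/10/5%: Σpᵢ³ = 0.2328, V = 236.6, detectable odds ratio 0.833.

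These use one set of proportions for both arms. Averaging over the arms, with slightly different assumed splits, gives 0.79 with 80% at 'none' and 0.83 with 60%.

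For a yes/no outcome of any disability, with assumed control prevalences of 10%, 20%, 30%, 40% and 50%, the detectable relative reductions are about 26%, 18%, 14%, 11% and 9%. The answer depends strongly on the endpoint, so Table 1 cannot stand in for it.

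**4. Does dichotomising lose power?** The same formula, for a true odds ratio of 0.75:

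| Assumed split | V, four levels | V, any v none | Power, four levels | Power, any v none |
|---|---|---|---|---|
| 80/10/5/5% | 150.1 | 148.0 | 94.1% | 93.8% |
| 60/25/10/5% | 236.6 | 222.0 | 99.3% | 99.0% |

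For any disability v none, almost nothing is lost. A moderate-or-severe cut on the first split would have 74.7% power, but the document does not choose that cut.

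**The case against.** The best defence is that a journal article condenses the full protocol, so the exact cut for prevalence may be fixed in a document not shown. That stands: a missing cut alone would be no finding. The text also does not prove that three distinct primary quantities exist. The prevalence to be analysed may be the four-level outcome dichotomised, or the three-or-more measure itself, since the power section calls its 5% a disability estimate. What no further document can cure is that the article lists a measure as secondary in one section and presents it as the primary measure in another.

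Three stronger readings are tempting and are not supported.

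- **That the primary outcome is underpowered.** The document gives no power calculation for it, which is a different matter. On the assumed splits above, the four-level outcome would detect odds ratios closer to 1 than a 5% yes/no outcome, for which the same formula gives V = 43.9 and a detectable odds ratio of 0.66.
- **That dichotomising throws away most of the power.** At an odds ratio of 0.75, a 5% yes/no outcome has 48% power, against 88% to 99% for four levels over the splits 85/8/4/3%, 80/10/5/5% and 60/25/10/5%. That gap comes mainly from the rarity of the 5% outcome, which is not a cut of the severity scale. The any-v-none comparison shows almost no loss.
- **That an endpoint could be picked after seeing the data.** The ambiguity leaves room for this, but nothing in the text indicates an intention, and the candidate measures are listed in advance.

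**Conclusion.** The concern holds as an inconsistency in what the protocol article calls primary. The stated 80% power belongs to secondary outcome 1, and the declared primary outcome has no detectable difference. The primary analysis does not say which levels it counts, and modelling by level is left to a sensitivity analysis.

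The contradiction rests on the text alone. The reproduction of Table 1 rests on a two-sided 5% test, equal groups at the factorial margin and independent children. The odds ratios of about 0.77 to 0.83 rest further on assumed level distributions and proportional odds, and are illustrations only. No claim is made that the study is too small, or that an any-v-none cut would lose material power.

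**What to change.** Before analysis, name one primary endpoint and use it consistently in the outcomes, power and analysis sections. Either route resolves the conflict:

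1. **Keep the four-level outcome as primary.** State its model: proportional odds on the four levels, or logistic regression at one named cut, with the other as sensitivity analysis. Relabel Table 1 as power for secondary outcome 1. Add a detectable difference for the primary outcome under a stated assumption on the level distribution.
2. **Make three or more affected attributes primary.** Table 1 then stands, and the outcomes list and the primary analysis change to match.

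In either case, say that the trend test over number of attributes affected is a separate analysis. A four-level proportional-odds model does not supply it, because it ranks children on a different scale.

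The cost is wording in three sections, plus one further power calculation under the first route. No new data are needed. A proportional-odds model brings reliance on its assumption, which can be covered by also reporting the comparison at each cumulative cut.

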### Analyses plan

The primary analysis will comprise comparison of MAHS disability prevalence by allocated treatment group, through fitting of logistic models including terms indicating allocation to Co-amoxiclav/not and to Erythromycin/not, together with an interaction term. Both HUI2 and HUI3 data will be collected and analysed as they have been designed to complement one another but are based on the same conceptual framework. HUI2 refers to worry and anxiety, HUI3 to happiness versus depression. Similarly while both refer to the degree of severity of pain, HUI2 focuses on the use of analgesia while HUI3 focuses on the disruption of activities. Self-care is only available in HUI2 and dexterity only in HUI3. Sensitivity analyses will include i) logistic modelling of the MAHS level of disability, ii) corresponding models for risk differences, iii) alternative approaches to analysing outcomes from multiple births, and iv) models adjusted for demographic covariates if their balance deteriorates during further follow up, and for other covariates including length of gestation, and year of KS1 assessment and original ORACLE outcomes.

Analyses of secondary outcomes will follow the approach for the primary outcome, appropriately modified where necessary to accommodate continuous or survival measures. Details of the analysis of KS1 data are to be developed in collaboration with colleagues in the agency responsible for collection and interpretation of these data. Explicit allowance for multiplicity of comparisons will be made in interpretation of the results.

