## Methods/Design

ORACLE was a double blind randomised controlled factorial design trial which evaluated whether giving broad spectrum antibiotics to women in SPL or with PROM improved neonatal mortality and morbidity.

Women were randomised to receive antibiotics and matching placebos 4 times daily for 10 days or until delivery, whichever was sooner. ORACLE tested Co-amoxiclav 375 mg and erythromycin 250 mg singularly and in combination.

This phase of the study – the MRC ORACLE Children Study – will follow-up children of women randomised to ORACLE at 7 years of age to determine whether antibiotics have effects on their development, educational attainment, and the risk of conditions such as cerebral palsy and respiratory illness. The MRC ORACLE Children Study will include the 8942 children born to those women randomised in the UK.

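### The primary logistic model includes the co-amoxiclav by erythromycin interaction without saying which effect is reported; with ordinary 0/1 terms the antibiotic coefficients are single-arm contrasts, which Table 1's 80% power does not cover

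*Protocol article*

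**What the plan says.** Under Methods/Design, the protocol article describes a factorial trial: "ORACLE tested Co-amoxiclav 375 mg and erythromycin 250 mg singularly and in combination". With placebo, that makes four randomised cells.

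Under Estimated power of study, it says "Table 1 demonstrates the differences detectable between any two intervention groups for the listed primary measure". The example in brackets is erythromycin against erythromycin-placebo, and the columns of Table 1 carry the same two labels. The table's caption says that, within PROM or SPL, "a response from 3700 babies will allow the following differences to be detected with 80% power". The outcome is three or more affected attributes, and "a conservative disability estimate of 5% has been taken as the principal estimate".

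Under Analyses plan, the primary analysis compares MAHS disability prevalence by allocated group through "logistic models including terms indicating allocation to Co-amoxiclav/not and to Erythromycin/not, together with an interaction term". Secondary outcomes are to follow the same approach. The section does not say whether the reported antibiotic effect is conditional on the other antibiotic being absent or averaged over it. It also does not say whether the interaction is a separate test.

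**The concern.** A term indicating that a drug was allocated or not is ordinarily a 0/1 indicator. With two such indicators and their product in a logistic model, the erythromycin coefficient is the log odds ratio for erythromycin when co-amoxiclav is zero, that is, erythromycin alone against double placebo. The co-amoxiclav coefficient is the mirror image. The two cells that received the other antibiotic do not inform that coefficient.

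The power section appears to rest on a different contrast: all children allocated erythromycin against all not allocated it. If the usual coefficient is read off the stated model, the reported effect has much less precision than the power statement implies. A null result could then be over-read as evidence against benefit or harm. The cohort is fixed by the original trial, so the precision cannot be regained by recruiting more children.

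**Working it through.** **Inputs**
- Responders per sub-group: 3700 (Table 1 caption). The text derives slightly more, "assuming an 85% response rate to a parental questionnaire": 4521 × 0.85 = 3843 (SPL) and 4421 × 0.85 = 3758 (PROM).
- Rates: 5% v 3.1%, 8% v 5.6% and 3% v 1.5% (Table 1).
- Assumed because not stated: two-sided α = 0.05; equal allocation, so 3700/2 = 1850 per margin and 3700/4 = 925 per cell; independent children (no clustering of multiple births).

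**Step 1. Which contrast reproduces Table 1?**

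Two-proportion power with pooled variance under the null:

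power = Φ{ [d − 1.96·√(2p̄(1−p̄)/n)] / √[(p₁(1−p₁) + p₂(1−p₂))/n] }

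For 5% v 3.1%, d = 0.019 and p̄ = 0.0405.
- n = 1850: (0.019 − 1.96 × 0.006482)/0.006474 = 0.973, so power is 83.5%.
- n = 925: (0.019 − 1.96 × 0.009166)/0.009156 = 0.113, so power is 54.5%.

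| Table 1 row | 1850 v 1850 | with continuity correction | 925 v 925 | with continuity correction |
|---|---|---|---|---|
| 5% v 3.1% | 83.5% | 81.3% | 54.5% | 49.8% |
| 8% v 5.6% | 82.7% | 80.9% | 53.6% | 49.9% |
| 3% v 1.5% | 86.8% | 84.3% | 58.5% | 52.3% |

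The margin reproduces the stated 80%: closely for the first two rows with continuity correction, and a little high for the third, which is consistent with rounded rates. The single-arm reading does not reproduce it.

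**Step 2. What the stated model estimates**

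Log odds ratio for 5% v 3.1%: ln(0.05/0.95) − ln(0.031/0.969) = 0.498.

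Variance of one cell's log odds is 1/[n·p(1−p)]. At n = 925 this is 0.0228 for 5% and 0.0360 for 3.1%. Suppose co-amoxiclav has no effect and there is no interaction.
- 0/1 coding with the interaction: SE = √(0.0228 + 0.0360) = 0.242. Wald power = Φ(0.498/0.242 − 1.96) = 53.7%.
- Same model, terms centred at −0.5/+0.5 (the average of the two erythromycin log odds ratios): SE = ½·√[2 × (0.0228 + 0.0360)] = 0.171. Power = Φ(0.498/0.171 − 1.96) = 82.8%.
- No interaction term: also SE 0.171 and 82.8%.

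The SE ratio is 0.242/0.171 = 1.41, or √2. For the other two rows, Wald power is 82.3% and 85.5% at the margin, against 53.2% and 56.9% for the 0/1 coefficient. A simulation of the four-cell trial (20,000 runs) gave 54%, 54% and 59% for the 0/1 coefficient, against 84%, 83% and 87% for the averaged contrast.

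**Step 3. Detectable difference at 925 v 925**

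Solving the Step 1 formula for 80% power gives 5% v 2.5% (relative reduction about 50%, against 38% in Table 1), 8% v 4.8% (40%, against 30%) and 3% v 1.15% (62%, against 50%).

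**The case against.** The strongest reply is that the article never states 0/1 coding, a reference cell or a reported contrast, and that such detail usually sits in an analysis plan that is not shown. It also speaks of models in the plural, which leaves room for a main-effects fit beside an interaction fit. Much of this stands. A reader might infer that half the children drop out of each main comparison, or that the interaction itself destroys the factorial efficiency. The documents do not support that: all responders enter the model, and Step 2 shows that the averaged effect from the same model keeps full power.

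A reader might also call the power section's phrase about any two intervention groups false. The bracketed example and the column labels show that the margin was meant, so the phrase is loose rather than false.

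Finally, Table 1 concerns three or more affected attributes. The power section treats this as the primary measure, but the outcomes section lists it as secondary. The article gives no assumed prevalence for the overall disability level, so 54% is not the power of the primary analysis as such.

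What remains is more than missing detail. The article states a primary model and states a power, and under the usual coding of that model the two do not refer to the same comparison.

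**Conclusion.** The point holds in a conditional form. Read with ordinary 0/1 indicators, the stated primary model yields single-arm antibiotic coefficients with about 54% power (range across Table 1's rows 53% to 59%, or about 50% to 52% with continuity correction). The marginal contrast on which Table 1 rests has about 83%. Read with centred terms or an averaged contrast, the same model meets the stated power. The text allows both readings, and they differ by about 30 percentage points. The figures rest on equal cells, a two-sided 5% level, no clustering of multiple births, and Table 1's rates and outcome. The documents do not support the conclusion that the primary analysis is underpowered as such. They support the conclusion that the effect to be reported must be named.

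**What to change.** In the Analyses plan, add one sentence: the primary effect of each antibiotic is its marginal effect, from a main-effects model or, if the interaction stays in, from centred (−0.5/+0.5) terms or a contrast averaged over the other antibiotic. State that the interaction is tested separately and that results for the four cells are shown alongside.

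In Estimated power of study, replace the reference to any two intervention groups with the marginal comparison of each antibiotic with its placebo.

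If single-arm effects are the intended target, leave the model as it is and restate Table 1 for about 925 per arm.

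The cost is one sentence in each section and no extra data. The drawback is that a marginal effect is harder to interpret if the interaction is large; the separate test and the four-cell results would show that.

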There is increasing evidence that, in addition to preterm birth, perinatal infection is an independent antecedent of other disability, particularly cerebral palsy and chronic lung disease. Therefore, perinatal administration of antibiotics could prevent neurological and respiratory disability by two mechanisms, either by prolonging pregnancy and/or by eliminating infection. In contrast however, it is possible that prolongation of pregnancy may increase rather than decrease the risk of disability by continuing fetal exposure to inflammatory cytokines, which have also been implicated in the genesis of neurological damage [4] and chronic lung disease [5]. Some clinical evidence to support this possibility comes from two observational studies of neurodevelopmental outcome in preterm infants born after PROM which showed a higher risk of cerebral palsy or neurological impairment compared with gestation matched controls [6,7]. In addition, duration of membrane rupture had a direct relationship with the risk of neurological impairment [7].

The cerebral and respiratory benefits reported with erythromycin in women with PROM in the ORACLE trial may have been secondary to (a) prolongation of pregnancy and (b) a reduction of the effects of fetal and neonatal lung infection or inflammation. Supportive evidence for the latter comes from broncho-alveolar lavage fluid studies. Studies of the constituents of broncho alveolar lavage fluid have shown that infants who develop chronic lung disease have higher concentrations of neutrophils [8], proinflammatory cytokines[9,10] and proxy markers of neutrophil recruitment, than those who recover from respiratory distress syndrome[9,11]. There is also evidence that intrauterine lung inflammation is implicated in the genesis of chronic lung disease, since high concentrations of the potent profibrotic agent, transforming growth factor, have been described in the first broncho-alveolar lavage fluid after birth of infants who go on to develop chronic lung disease [5,12]. The MRC ORACLE Children Study provides a unique opportunity to determine whether the reductions in chronic lung disease found at discharge from hospital in the erythromycin group are reflected in a decreased incidence of respiratory disease and the need for therapy at 7 years of age.

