### Planned subgroup analyses

Comparisons of primary and secondary outcomes will be undertaken for the infants of women with: (1) SPL – intact membranes; (2) PROM; (3) multiple & singleton pregnancies; (4) >32 week gestation and < 32 week gestation; (5) > < 28 weeks gestation.

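### Sensitivity analysis (iv) adjusts for length of gestation and the original ORACLE outcomes, which arise after randomisation and lie on the stated causal route, so it cannot test the robustness of the total treatment effect

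*Protocol article*

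**What the plan says.** The Analyses plan of the Protocol article sets the primary analysis as "logistic models including terms indicating allocation to Co-amoxiclav/not and to Erythromycin/not, together with an interaction term". It lists no covariates for that model.

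Four sensitivity analyses follow. The fourth has two parts. The first is "iv) models adjusted for demographic covariates if their balance deteriorates during further follow up". The second is adjustment "for other covariates including length of gestation, and year of KS1 assessment and original ORACLE outcomes". The balance condition belongs to the demographic covariates; the second part carries no condition, and nothing marks it as explanatory. The next paragraph extends the scheme: "Analyses of secondary outcomes will follow the approach for the primary outcome", with modification for continuous or survival measures.

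Background & Rationale gives the hypothesis: "perinatal administration of antibiotics could prevent neurological and respiratory disability by two mechanisms, either by prolonging pregnancy and/or by eliminating infection". It says of the benefits seen with erythromycin in PROM that they "may have been secondary to (a) prolongation of pregnancy and (b) a reduction of the effects of fetal and neonatal lung infection" or inflammation. It also makes it a study question whether less chronic lung disease at discharge leads to less respiratory disease at 7 years.

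Planned subgroup analyses lists "4) >32 week gestation and < 32 week gestation; (5) > < 28 weeks gestation" and does not say when gestation is measured.

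**The concern.** A sensitivity analysis of a randomised comparison should estimate the same quantity as the primary analysis under different assumptions. Here that quantity is the total effect of allocation on the child at 7 years, by whatever route. A model that conditions on something the treatment changes estimates a different quantity. Listed beside risk-difference models and alternative handling of multiple births, it will be read as a check on the main result.

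Two errors of interpretation could follow. A real benefit acting through longer gestation or less neonatal lung disease could shrink on adjustment and be called fragile. Alternatively, the adjusted estimate could move in either direction because infection, or another shared cause, affects both the adjusted variable and the 7-year outcome. The respiratory outcome is the clearest case: adjusting it for neonatal chronic lung disease conditions on the very link that the Background sets out to examine.

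**Working it through.** **1. Timing and role of each covariate in the second part of (iv)**

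| Covariate | When it is fixed | What the Background reports |
|---|---|---|
| Original ORACLE outcomes (death, major cerebral abnormality before discharge, chronic lung disease) | After randomisation, without ambiguity | Composite improved with erythromycin in singletons after PROM; no neonatal improvement with either drug in SPL |
| Length of gestation | At delivery, in the ordinary sense | Prolongation associated with erythromycin and with co-amoxiclav; named as a route of action |
| Year of KS1 assessment | Mainly by date of birth | Not named as a route; not part of this point |

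The first row is sufficient for the point. The second supports it on the usual meaning of the term.

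**2. What the adjusted coefficient means**

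Write T for allocation, M for gestation at delivery or a neonatal outcome, and Y for disability at 7 years. The primary model, shown for one drug, is logit P(Y) = a + bT, and b is the total effect. The model in (iv) is logit P(Y) = a' + b'T + cM. If T changes M and M changes Y, b' leaves out what passes through M. If an unmeasured U (for example infection) affects both M and Y, conditioning on M links T to U, and b' is not a clean direct effect either.

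**3. Illustration of direction only**

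Every parameter here is invented; none comes from the documents. One million children were simulated with T randomised 1:1 and M = 0.3T − 0.5U + noise, where U and the noise each have SD 1. The log odds of Y were −3.2 − 0.8M + gU, with no direct effect of T.

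- g = 0 (U does not affect Y): risks 4.3% v 5.4%, unadjusted OR 0.80, OR adjusted for M 1.00. The whole effect disappears.
- g = 0.8 (U also affects Y): risks 6.6% v 8.0%, unadjusted OR 0.81, OR adjusted for M 1.09. The direction reverses.

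In both cases the true total effect is a benefit.

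**4. The plan's own figures**

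The article gives no figure for this analysis. Table 1 states 80% power for 5% v 3.1% with 3700 responses. Assuming an equal split (3700/2 = 1850 per side) and a two-sided 5% level, this gives 81.3% with continuity correction and 83.5% without, consistent with the stated value. That calculation compares two groups without covariates, and the present point does not depend on it.

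**5. Subgroups**

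The cuts at 32 and 28 weeks could use gestation at entry or at delivery. The choice matters. When the same simulation was cut at the lowest 30% of M, the treated share was about 42% in the short stratum and 53% in the long one, so the strata would no longer be balanced by randomisation. Gestation at entry has no such problem.

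**The case against.** The strongest reply is that these are sensitivity analyses only. The main estimate comes from a model with allocation terms alone, so no primary result is biased. That stands and limits the point. A reader might infer from the list in (iv) that the plan's main treatment effect is adjusted for mediators; the Analyses plan does not say so.

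Second, the reported treatment effects on neonatal outcomes concern PROM. In SPL the Background reports no neonatal improvement with either drug, and SPL supplies 4521 of the 8942 children. This also stands. Where treatment does not change a covariate, adjusting for it removes little, so the concern is strongest for PROM.

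Third, models containing neonatal outcomes have a legitimate use, since the Background asks whether the lung benefit persists to age 7. That is true, but it argues for naming them as explanatory, not for listing them as sensitivity analyses.

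Fourth, the subgroup text does not show a flaw. SPL and PROM are entry conditions, so gestation at entry is a natural reading, and the inequality signs look like shorthand. A reader might infer that infants are to be compared within birth-gestation strata, or that those at exactly 32 or 28 weeks are to be left out. The text establishes neither.

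Last, it is tempting to express the harm as lost power. That would need the share of the effect passing through gestation or neonatal morbidity, which the documents do not give, and a standard error for the adjusted model. It would also describe a sensitivity model, whereas the trial's power rests on the primary comparison.

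**Conclusion.** The point holds for sensitivity analysis (iv). As written, it plans adjustment for variables that arise after randomisation and that the article itself places between treatment and outcome. The resulting estimates cannot confirm or undermine the total effect.

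The size cannot be derived from the documents; the simulation shows only that attenuation to no effect, or reversal, is possible. The conclusion rests on reading length of gestation as duration to delivery. If it meant gestation at trial entry, that covariate would be acceptable, and the objection to the original ORACLE outcomes would remain. The subgroup basis is an ambiguity to settle, not an error. This is a wording correction worth making before the results are analysed, and it leaves the primary analysis as it is.

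**What to change.** In the Analyses plan, item (iv):

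- Restrict covariates in models of the total treatment effect to variables fixed before randomisation. Replace length of gestation with gestation at trial entry, and remove the original ORACLE outcomes from the list.
- Add a sentence that any model containing gestation at delivery or neonatal outcomes is an exploratory mediation analysis, reported separately and not used to judge the robustness of the main result.
- Apply the same rule to the secondary outcomes, which inherit the approach.

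In Planned subgroup analyses, as a clarification, state that gestation is taken at trial entry and assign each boundary week to one stratum, for example below 32 v 32 and above, and below 28 v 28 and above.

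The cost is wording only. It assumes that the parent trial recorded gestation at entry; if so, no new data are needed. The explanatory models remain available under their proper label.
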